### Sample size

The overall sample size for the study is based on the assessment of hypertension prevalence. Assuming a prevalence of hypertension of 25–35%, as detected by the reference standard method (24-hr-ABPM), we will require 832–1003 participants to generate validity parameters for hypertension prevalence with a precision of ±3% overall and ±5% at each of the two sites
^
24,
41
^. We have made a provision for loss of data in 25% of participants due to poor data quality, taking the total number of participants required to 1250, equally divided between Kilifi (N=625) and Kiang West (N=625). This overall sample size will provide sufficient statistical power to address the other aims stated above.

In our assessment of BP and risk factors, and assuming for illustrative purposes that 10% of individuals will have any of the putative factors and that the standard deviation of systolic blood pressure will be 15 mmHg, then 1,003 participants will provide at least 80% statistical power for an alpha of 0.05 to detect a 4mm Hg difference in systolic BP in those with and without the exposure of interest.

Assuming a prevalence of hypertension detected by the reference standard method (24-hr-ABPM) of 30%, we estimate that approximately 300 participants from those recruited in Objective 1 will be classified as hypertensive. With 300 hypertensive patients, we would be able to estimate the confidence interval for a conservative HMOD prevalence of 35% with lower and upper intervals of 29.7% and 40.4% respectively, and that we will have over 95% power for an alpha of 0·05 to test the null hypothesis that the prevalence of HMOD is below 25%. To further explore the difference in the prevalence of HMOD in the hypertensive and general population, we intend to assess all participants recruited into the study for HMOD.

When measured with the reference standard techniques, we expect a 35% prevalence of HMOD among the 300 estimated hypertensive participants and approximately 5% prevalence in the remaining non-hypertensive participants. This will provide us with a total available sample of 153 participants with HMOD. Assuming at least 85% sensitivity of detection of HMOD by the POC strategies we will have at least 80% power for an alpha of 0.05 to test the null hypothesis that the sensitivity is below 75%. As above, we will conduct POC HMOD assessments on all participants.

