**Figure 3. f3:**
[figure not shown]
Schematic overview of blood pressure measurements performed in each participant.

**
*Hypertension mediated organ damage assessment*.** We will measure HMOD in the following organ systems: heart, eye, kidney, and vasculature. All measurements will be conducted during an in-clinic visit. The prevalence of HMOD will be assessed using reference-standard clinical assessments. In addition, we will validate the accuracy of POC assessments for HMOD compared to the reference-standard methods for the heart, eyes, and kidney. For all HMOD assessments, a detailed SOP will be used to ensure consistency between both study sites (Kenya and The Gambia) and staff will be trained in the relevant competencies. HMOD definitions in all categories will follow existing clinical guidelines
^
22
^. These assessments are summarised here and described in
Figure 4 and
Table 2 and
Table 3.

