### Statistical analysis plans

A detailed statistical analysis plan will be produced before data collection is completed and uploaded to a public repository. A summary of statistical analysis approaches that will be taken for this study is outlined here.

**
*Hypertension prevalence*.** We will estimate sensitivity; specificity; positive and negative predictive values; and the positive and negative likelihood ratios of each BP measurement approach compared to the reference standard 24-hour BP measurement method.

**
*Identifying hypertension risk factors*.** The primary outcome will be hypertension, defined as a BP of >140/90mmHG using 24-hour BP measurement, or ongoing therapy with anti-hypertensives. We will determine the relationship between the candidate risk factors and blood pressure and hypertension using multivariate linear and logistic regression methods as appropriate. We will include confounders in the regression models based on results of univariate models and existing literature on the subject.

**
*Prevalence of organ damage*.** We will analyse the overall prevalence of HMOD and report age- and sex-standardised and stratified prevalence rates. We will also analyse prevalence rates stratified by type of HMOD (left ventricular hypertrophy, impaired left ventricular systolic function, renal dysfunction, hypertensive retinopathy, or arterial stiffness). Finally, we will construct logistic regression models to identify the participant parameters associated with presence of HMOD.

**
*Accuracy of POC diagnostic tools*.** The diagnostic accuracy of the POC assessments will be estimated using sensitivity; specificity; positive and negative predictive values; and positive and negative likelihood ratios of each POC parameter compared to the conventional measurement. These comparisons will be:

1) Left ventricular systolic function: Smartphone-based ECG (analysed with Mayo Clinic trained AI algorithms) compared to transthoracic echocardiogram (reference standard).2) Left ventricular hypertrophy: Smartphone-based ECG (analysed with validated and trained AI algorithms) compared to 12-lead ECG and transthoracic echocardiogram (reference standard).3) Hypertensive retinopathy: Smartphone-based retinal imaging compared to clinical grade retinal camera (reference standard) in detecting HMOD.4) Renal dysfunction: POC clinical chemistry and urinalysis dipstick compared to conventional clinical laboratory assessment of blood and urine markers for renal function

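### The 80% power for point-of-care sensitivity is worked out on pooled HMOD cases (153, from mixed denominators), but the listed accuracy comparisons are organ by organ, so that power is shown for none of them

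*Protocol article*

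**What the plan says.** The Sample size section starts from hypertension prevalence: "we will require 832–1003 participants to generate validity parameters for hypertension prevalence", with a 25% provision for data loss "taking the total number of participants required to 1250". It goes on: "Assuming a prevalence of hypertension detected by the reference standard method (24-hr-ABPM) of 30" per cent, "approximately 300 participants from those recruited in Objective 1 will be classified as hypertensive". It then applies an HMOD prevalence of 35% to those 300 and about 5% to the remaining non-hypertensive participants, and concludes: "This will provide us with a total available sample of 153 participants with HMOD".

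The power statement follows: "Assuming at least 85% sensitivity of detection of HMOD by the POC strategies we will have at least 80% power", at an alpha of 0.05, against a null sensitivity below 75%. Whether the test is one- or two-sided is not stated.

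Under Study procedures, the protocol says "we will validate the accuracy of POC assessments for HMOD compared to the reference-standard methods for the heart, eyes, and kidney". Table 2 marks the point-of-care technique for arterial stiffness as not applicable. Under Statistical analysis plans, arterial stiffness is one of five HMOD types. Accuracy there covers sensitivity, specificity, predictive values and "positive and negative likelihood ratios of each POC parameter compared to the conventional measurement". Four comparisons are listed: left ventricular systolic function, left ventricular hypertrophy, retinopathy and renal dysfunction.

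**The concern.** Two things do not fit together. First, 300 hypertensives at 30% prevalence imply a sample of about 1,000, and the non-hypertensives left in that sample cannot bring the total to 153.

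Second, and more important, a sensitivity has as its denominator the participants positive on that test's own reference. For the retinal camera these are the participants with reference-standard retinopathy, not everyone with any HMOD. The power is therefore worked out for a pooled condition that is not among the listed comparisons. The pool also contains participants whose only damage is arterial stiffness, which no point-of-care device in the study assesses.

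At stake is how firmly each device can be judged. The protocol says its sample size gives adequate power for the other aims, and the point-of-care assessments also feed the cost-effectiveness model. Readers would expect more certainty about each device than the case numbers may support.

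**Working it through.** **Inputs** (Sample size section): 30% hypertensive, about 300 people; 1,003 evaluable at the upper end; 1,250 enrolled; HMOD prevalence 35% and 5%; sensitivity 85% against 75%; alpha 0.05. I take 35% and 5% as prevalences of any HMOD. The section says only HMOD, but the analysis section separates overall prevalence from prevalence by type.

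**Step 1: the case count** (cases = 0.35 × hypertensives + 0.05 × non-hypertensives)

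- Protocol's figure: 300 × 0.35 + (1,250 − 300) × 0.05 = 105 + 47.5 = 152.5, printed as 153.
- Evaluable base, 1,003: 300 × 0.35 + 703 × 0.05 = 105 + 35.15 = 140.
- Enrolled base, 1,250: 375 × 0.35 + 875 × 0.05 = 131.25 + 43.75 = 175.

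Neither base gives 153.

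**Step 2: power for the pooled count.** One-sample test of a proportion, with the null variance for the critical value and the alternative variance for power:

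power = 1 − Φ[(0.75 + z·√(0.75 × 0.25/n) − 0.85) / √(0.85 × 0.15/n)], with z = 1.96 (two-sided) or 1.645 (one-sided).

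| Cases | Two-sided (exact) | One-sided (exact) |
|---|---|---|
| 153 | 86.2% (84.8%) | 92.9% (92.7%) |
| 140 | 82.6% (79.9%) | 90.6% (90.1%) |
| 175 | 90.8% (90.4%) | 95.6% (93.4%) |

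The stated power of at least 80% is reproduced at 153, and it essentially survives at 140.

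**Step 3: reference-positives needed in one comparison for 80% power**

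n = [(z·√(0.75 × 0.25) + 0.842·√(0.85 × 0.15)) / 0.10]²

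- Two-sided: [(0.849 + 0.301)/0.10]² ≈ 132.1, rounded up to 133. This is 133/140 = 95% of the evaluable-base cases, or 133/175 = 76% of the enrolled-base cases.
- One-sided: [(0.712 + 0.301)/0.10]² ≈ 102.6, rounded up to 103. This is 103/140 = 74%, or 103/175 = 59%.

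That share of all HMOD cases would have to be positive for the same condition, and for all four conditions if the claim is to cover all four comparisons.

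**Step 4: illustrations.** The protocol gives no organ-specific prevalence, so the case numbers are assumptions. 70 is half of 140; 28 is 140/5, meaning five equal types without overlap. The half-width is 1.96 × √(0.85 × 0.15/n).

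| Assumed cases | Two-sided power | One-sided power | 95% CI half-width at 85% |
|---|---|---|---|
| 105 | 69% | 81% | ±7 points |
| 70 | 49% | 64% | ±8 points |
| 50 | 35% | 49% | ±10 points |
| 28 | 19% | 30% | ±13 points |

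**The case against.** Three stronger readings are tempting, and the protocol does not support them.

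- **That 153 is inflated and 140 is the right number.** All participants are to have the HMOD and point-of-care assessments. The data-loss provision is attached to the prevalence calculation, and nothing says that someone with unusable 24-hour readings is lost to Objective 4. On the enrolled base the count is 175, so 153 is inconsistent but lies between two consistent values. Nor should 140 be reduced by a further 25%, because 1,003 is already the number left after the provision.
- **That the miscount breaks the power claim.** It does not: 140 cases give about 80% to 83% two-sided and about 90% one-sided.
- **That none of the four comparisons can reach 80%.** This cannot be proved. Organ prevalences and overlap between organs are not given. The null is worded in one direction, so a one-sided test is possible, and 103 cases would then be enough.

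It can also be said that this calculation did not set the sample size, and that the analysis section plans to estimate accuracy and lists no test against 75%. Both are true, and both lower the severity. Objective 4 is worded as identifying patients with HMOD, and a composite may appear in the fuller analysis plan, which is not shown. Even so, the article itself gives a case count and a power figure, and they do not match the comparisons it lists.

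**Conclusion.** The point holds as a mismatch between the power statement and the listed analyses, with a secondary arithmetic slip. The stated power applies to pooled HMOD and is shown for no listed comparison. One comparison would need 74% to 95% of 140 cases, or 59% to 76% of 175, to share the same condition, depending on sidedness. Power is therefore probably well below 80% for the rarer types. That last step is a judgement: it rests on assumed case numbers and on reading 35% and 5% as any-HMOD prevalences. Severity is moderate, since the sample size was fixed by hypertension prevalence and limited case numbers would widen the intervals rather than bias the estimates.

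**What to change.** Compute the HMOD case count on one stated base (140 on the evaluable base that yields the 300 hypertensives) and state whether the test is one- or two-sided. Then choose one of two courses:

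1. Pre-specify a composite comparison, any heart, eye or kidney HMOD by point-of-care against the same by reference standard. Leave out participants whose only damage is arterial stiffness, recompute the count, and attach the power to this comparison. From 140 there is room to lose only 140 − 133 = 7 cases two-sided, or 140 − 103 = 37 one-sided, before power drops below 80% by the normal approximation.
2. Drop the power claim for the organ-level comparisons and give the expected confidence interval width for each one over an assumed range of prevalence.

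The cost is wording and a short calculation, plus one derived variable under the first course. No new data are needed. The downside is that the organ-level claims become more modest.

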### Study procedures

**
*Baseline assessments*.** Baseline assessments will collect information including demographics, household assets, anthropometrics, diet, physical activity, history of hypertension and medication use for hypertension and other diseases (
Table 3).

**
*Blood pressure assessment*.** We will conduct a cross-sectional study over two weeks to determine the accuracy of three BP measurement methods compared to the reference standard of 24-hour Ambulatory BP Measurement (24-hr-ABPM). The alternative BP measurement methods are: 1) Attended Automated BP Measurements (aABPM); 2) Unattended Automated BP Measurements (uABPM); and 3) Home-Based BP Measurement (HBPM). Details for all BP measurement methods are summarised in
Table 1 and
Table 3.

All BP measurements will be conducted by CHWs trained by the study team to perform the blood pressure measurements based on study SOPs. The competencies of the CHWs will be assessed by the study team prior to data collection and at regular intervals during data collection. The CHWs will then collect blood pressure measurements in a random order at participants’ homes. The random order of blood pressure measurements for each of the participants will be set using a computer-generated randomisation list produced prior to measurements starting.

Each participant is expected to have completed all four BP measurements over a two-week period. A schematic overview of the procedure is shown in
Figure 3. We will follow relevant international cardiological society guidelines for conducting all BP measurements
^
45–
47
^.

**Figure 3. f3:**
[figure not shown]
Schematic overview of blood pressure measurements performed in each participant.

**
*Hypertension mediated organ damage assessment*.** We will measure HMOD in the following organ systems: heart, eye, kidney, and vasculature. All measurements will be conducted during an in-clinic visit. The prevalence of HMOD will be assessed using reference-standard clinical assessments. In addition, we will validate the accuracy of POC assessments for HMOD compared to the reference-standard methods for the heart, eyes, and kidney. For all HMOD assessments, a detailed SOP will be used to ensure consistency between both study sites (Kenya and The Gambia) and staff will be trained in the relevant competencies. HMOD definitions in all categories will follow existing clinical guidelines
^
22
^. These assessments are summarised here and described in
Figure 4 and
Table 2 and
Table 3.

**Figure 4. f4:**
[figure not shown]
Schematic overview of hypertension-mediated organ damage measurements performed in each participant for Objectives 3 and 4.

**Table 2. T2:** Overview of the methods used to measure hypertension mediated organ damage.

Type of hypertension mediated organ damage	Reference-standard assessment technique	Point-of-care assessment technique
**Left ventricular hypertrophy**	*Transthoracic echocardiogram and 12-lead ECG*	*Smartphone based 6-lead ECG*
**Left ventricular systolic function**	*Transthoracic echocardiogram*	*Smartphone based 6-lead ECG*
**Hypertensive Retinopathy**	*Clinical grade retinal cameras*	*Smartphone-based portable retinal camera*
**Renal dysfunction**	*Clinical laboratory assessment of whole blood * *and urine*	*Point-of-care clinical chemistry devices and * *urine dipstick*
**Arterial stiffness**	*Blood pressure cuff-based measurement of pulse* *wave velocity*	*Not applicable*

**Table 3. T3:** Summary of all planned study procedures.

	Visit 1: Consent and baseline	Visits 2–4: BP measurements	Visit 5: HMOD assessment	Visit 6: Results feedback
**Eligibility assessment**	X			
**Informed consent**	X			
**Baseline questionnaires** ** - Clinical history** ** - Demographic variables** ** - Anthropometrics** ** - Treatment BP** ** - Household assets** ** - Dietary history** ** - Physical activity**	X		X	
**24-hr-ABPM**		X		
**aABPM**		X		
**uABPM**		X		
**HBPM**		X		
**BP measurement ** **acceptability questionnaire**			X	
**12-lead ECG**			X	
**Transthoracic ** **echocardiogram**			X	
**Clinical grade retinal ** **scanning**			X	
**Clinical laboratory ** **assessment of whole blood** ** and urine**			X	
**Urine dipstick**			X	
**Smartphone-based ECG**			X	
**Smartphone-based** ** fundoscopy**			X	
**Point-of-care clinical ** **chemistry**			X	
**Blood pressure cuff ** **measurement of pulse wave ** **velocity**			X	
**aABPM verification**			X	
**uABPM verification**			X	
**Participant result feedback**				X

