**Reference standard HMOD assessment**

In the heart, left ventricular systolic dysfunction will be assessed with a transthoracic echocardiogram (TTE), and left ventricular hypertrophy will be assessed with a TTE and 12-lead electrocardiogram (ECG). In the eye, hypertensive retinopathy will be assessed from retinal images captured by a fixed retinal camera and graded for hypertensive retinopathy by trained staff. Kidney dysfunction will be assessed using clinical laboratory assessment of blood and urine to measure serum creatinine levels and estimate glomerular filtration rate (eGFR) and glomerular function using urine albumin:creatinine ratio and proteinuria. Finally, we will assess pulse wave velocity and arterial stiffness using a specialised blood pressure cuff (Arteriograph, TensioMed, Hungary).

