**Point-of-care HMOD assessment**

Point-of-care assessment of left ventricular systolic dysfunction and left ventricular hypertrophy will be assessed using a mobile phone based 6-lead ECG (KardiaMobile, AliveCor, United States of America) coupled with artificial intelligence (AI) tools developed for ECG analysis
^
48
^. In the eye, we will assess hypertensive retinopathy using a handheld, mobile phone based, non-mydriatic retinal camera (Remidio, India). Retinal image grading will be conducted by the same staff who graded the reference standard images. Finally, kidney dysfunction (defined as serum creatine levels, eGFR and glomerular function) will be measured using urine dipsticks, and POC clinical chemistry devices (Abbott iStat, Abbott, United States).

**
*Genetic sampling*.** For the genetic analyses, DNA will be extracted from whole blood samples using Qiagen DNA Blood Mini kit. DNA extraction will make use of blood samples drawn for HMOD measurement and no new blood sample is required. We will then use PCR to determine presence of the genotypes of interest, including malaria and trypanosomiasis protective polymorphisms (Dantu, SCT, APOL1 or APOL2)
^
36,
37
^. These analyses will be conducted in KWTRP.

**
*Health economics assessment*.** We will use the human capital approach to collect primary data on patient costs including the opportunity cost of time spent administering blood pressure-monitoring methods, missing productive activity and any out-of-pocket costs incurred for undergoing study procedures. Health system cost data will be collected using a micro-costing, ingredient-based approach. Data will be collected from a structured questionnaires administered to three CHWs from each study site, structured observations of CHW and user time spent on BP and HMOD measurement, and a survey using a structured questionnaire to 200 individuals diagnosed with hypertension
^
49
^.

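### Objective 4, LVH comparison: a reference standard that includes the 12-lead ECG is likely to share errors with the 6-lead smartphone ECG and would bias its sensitivity and specificity

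*Protocol article*

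**What the plan says.** Three places in the protocol article describe the LVH reference.

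- **Table 2**, reference-standard column, LVH row: "Transthoracic echocardiogram and 12-lead ECG". The point-of-care column of the same row has "Smartphone based 6-lead ECG".
- **Reference standard HMOD assessment**: "left ventricular hypertrophy will be assessed with a TTE and 12-lead electrocardiogram (ECG".
- **Statistical analysis plans**, accuracy of POC diagnostic tools, item 2: "Smartphone-based ECG (analysed with validated and trained AI algorithms) compared to 12-lead ECG and transthoracic echocardiogram (reference standard".

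The smartphone recording is "coupled with artificial intelligence (AI) tools developed for ECG analysis" (Point-of-care HMOD assessment). For left ventricular systolic function the same device is judged against echocardiography alone, in Table 2 and again in item 1 of the accuracy list: "Smartphone-based ECG (analysed with Mayo Clinic trained AI algorithms) compared to transthoracic echocardiogram (reference standard".

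The article does not say whether the two LVH tests form one status or serve in two separate comparisons. It refers definitions elsewhere: "HMOD definitions in all categories will follow existing clinical guidelines".

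**The concern.** Sensitivity and specificity mean what they claim only if the reference does not make the same mistakes as the test being judged. A 12-lead and a 6-lead surface ECG record the same electrical activity in the same person, and Table 3 places both at the same visit. Increased ventricular mass without an ECG change tends to be missed by both. An ECG change without increased mass tends to be flagged by both. If the 12-lead ECG helps decide who has LVH, some of those joint errors are scored as correct results for the smartphone device.

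At stake is one of the four named accuracy comparisons in Objective 4. A reader deciding whether the smartphone ECG can replace echocardiography for LVH could be misled about how well it does so.

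**Working it through.** **The plan's own figures.** The article gives no figure for LVH. The nearest is the overall HMOD count: "This will provide us with a total available sample of 153 participants with HMOD". It reproduces: 0.35 × 300 + 0.05 × (1250 − 300) = 105 + 47.5 = 152.5, or 153. With n = 153, power for a sensitivity of 85% against a null of 75% is 86.2% (two-sided, normal approximation), consistent with the stated minimum of 80%. These figures are not in dispute and say nothing about LVH alone.

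**Set-up.** TTE is taken as the truth. All inputs below are assumptions, since the documents give none of them.

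- π = LVH prevalence on TTE = 0.15
- 12-lead ECG: sensitivity e = 0.30, false-positive rate f = 0.10
- Smartphone ECG: true sensitivity s, false-positive rate g
- q = share of 12-lead false positives that the smartphone ECG also flags
- r = share of 12-lead true positives that the smartphone ECG also flags

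**Either-positive rule**

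- Apparent sensitivity = [πs + (1 − π)f q] / [π + (1 − π)f]
- Apparent specificity = 1 − (g − f q)/(1 − f)

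**Both-positive rule**

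- Apparent sensitivity = r
- Apparent specificity = 1 − [π(s − e r) + (1 − π)g] / (1 − πe)

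**Case A: true accuracy 30%/90%, overlap 80%**

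- Either: (0.045 + 0.068)/0.235 = 0.113/0.235 = 48%; specificity 1 − 0.02/0.90 = 98%.
- Both: 0.036/0.045 = 80%; specificity 1 − (0.009 + 0.085)/0.955 = 90%.
- With overlap 60%, apparent sensitivity is (0.045 + 0.051)/0.235 = 41% (either) or 60% (both).

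**Case B: true accuracy 85%/85%**

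- Either, q = 0.60: (0.1275 + 0.051)/0.235 = 76%; specificity 1 − (0.15 − 0.06)/0.90 = 90%.
- Either, q = 0.80: (0.1275 + 0.068)/0.235 = 83%; specificity 1 − (0.15 − 0.08)/0.90 = 92%.
- Both: sensitivity is r. At r = 0.85 specificity is 1 − (0.08925 + 0.1275)/0.955 = 77%. At r = 1 it is 1 − (0.0825 + 0.1275)/0.955 = 78%.

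**Two effects at work.** Under the either-positive rule, apparent sensitivity is a weighted average of s and q. It exceeds the true value only if q is greater than s. To isolate the effect of shared error, set q = g, which is independence among people without LVH:

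| Either-positive rule | True | Independent errors | Shared errors |
|---|---|---|---|
| Case A (q = 0.80) | 30%/90% | 0.0535/0.235 = 23%, specificity 90% | 48%/98% |
| Case B (q = 0.60) | 85%/85% | 0.14025/0.235 = 60%, specificity 85% | 76%/90% |

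Shared error raises both measures compared with independent errors. Separately, 12-lead false positives enter the diseased group and pull sensitivity down. The net result depends on which effect is larger.

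**A second set of assumptions** gives the same picture: prevalence 12%, smartphone ECG truly 75%/85%, 12-lead ECG 30%/90%, errors correlated at ρ.

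| Rule | ρ = 0 | ρ = 0.3 |
|---|---|---|
| Either | 50%/85% | 63%/89% |
| Both | 75%/80% | 95%/81% |

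**The case against.** **The composite is not stated.** Item 2 of the accuracy list could mean two separate comparisons, or could attach the reference-standard label to echocardiography only. On either reading the comparison with TTE is free of this bias. That is possible, and it is why the point is conditional on a composite. But Table 2 and the reference-standard section list both tests without distinction, so it is not their plain reading. If it is what was meant, the correction is the same.

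**The combination rule may be in the SAP, an SOP or the cited guideline.** This stands, and the absence of a rule here is not a fault. The point is the stated presence of the 12-lead ECG in the reference. Choosing either-positive or both-positive would not remove the shared error.

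**The amount of overlap is unknown.** This also stands. The index test is a 6-lead trace read by AI tools, and the article gives neither their training target nor any 6-lead/12-lead agreement. Some correlation is likely; 60% and 80% are illustrations.

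**Inferences that go too far.** A reader might conclude that the smartphone ECG's accuracy will be inflated. Case B shows sensitivity falling under the either-positive rule, and specificity falling under the both-positive rule. A reader might also conclude that LVH prevalence in Objective 3 is wrong. That presumes echocardiography alone defines LVH, whereas definitions are referred to a guideline not shown, and the shared-error argument needs an index test, which a prevalence estimate lacks. Nor is it stated that the bias enters the cost-effectiveness model. That section takes costs from primary data and outcomes from secondary sources, and does not name Objective 4 accuracy as an input.

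**Conclusion.** The concern holds for the LVH comparison in Objective 4. The article places the 12-lead ECG in the reference standard for another ECG, and any composite built on it would be expected to bias the smartphone ECG's sensitivity and specificity. The direction and size cannot be fixed from the documents. In the two worked cases apparent sensitivity ranges from 18 points above the true value (48% against 30%, either-positive) or 50 points above (80% against 30%, both-positive) to 9 points below (76% against 85%, either-positive). These figures rest on an assumed prevalence, assumed 12-lead and smartphone accuracy, assumed overlap, and TTE taken as the truth.

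The comparisons for systolic function, retinopathy and renal function are not affected. No conclusion is drawn about Objective 3 prevalence, the cost-effectiveness results or the lack of a stated combination rule.

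**What to change.** In the LVH row of Table 2, in the section on reference-standard HMOD assessment and in item 2 of the accuracy list, name TTE alone as the reference standard for the LVH accuracy analysis, matching what is already done for systolic function. Report the 12-lead ECG separately in two ways: as a second index test against TTE, and as 6-lead versus 12-lead agreement.

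No new data are needed, because the article plans reference and point-of-care HMOD assessment for all participants. The article also says that the detailed SAP will be produced before data collection is completed, so the change can be carried into it. The one real cost is that LVH status will be missing for participants whose echocardiogram cannot be read; their number should be reported.
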